**Methods:**

This is a 2-arm individually randomized controlled trial comparing IMARA to a family-based control program matched in time and intensity with 525 15–19-year-old Black South African AGYW and their FC-dyads in Cape Town’s informal communities. AGYW will complete baseline, 6-, and 12-month assessments. Following randomization, AGYW-FC dyads will participate in a 2-day group workshop (total 10 h) that includes joint and separate mother and daughter activities. Primary outcomes are AGYW STI incidence, HTC uptake, and PrEP uptake at 6 months. Secondary outcomes are AGYW STI incidence, HTC uptake, and PrEP uptake at 12 months, sexual behavior (e.g., condom use, number of partners), HIV incidence, and ART/PrEP adherence and intervention cost-effectiveness. AGYW who test positive for a STI will receive free treatment at the study site. HIV positive participants will be referred to ART clinics.

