### Study objectives

The purpose of this study is to test the effectiveness and cost-effectiveness of a culturally-tailored, evidence-based, HIV/STI prevention program for SA AGYW and FC. We will randomly assign 525 AGYW-FC dyads to IMARA-SA (*n* = 263) or a family-based health promotion (HP) program (*n* = 262) matched in time and intensity and compare participants on incident STI, and HTC and PrEP uptake at 6 months. Secondary objectives are to assess intervention effects on the primary outcomes at 12 months, reported non-condom use, number of partners, HIV incidence, and adherence to ART/PrEP. We will also evaluate the costs and CE of IMARA with respect to the acquisition of STI and HIV where possible, considering power limitations.

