### Randomization

We will use a 1:1 randomization allocation to assign FC-AGYW dyads to treatment arm (IMARA-SA *n* = 263 or HP *n* = 262) following the baseline assessment. The AGYW will select a colored paper from a hat that determines the family’s group assignment. Assessors but not intervention staff will be blinded to treatment arm at 6- and 12-month follow-up.

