### Intervention delivery

Interventionists will be South African, female, and Black or mixed race to match AGYW and FC. Both interventions will be delivered over two sessions (about 10 h of content). We will enroll approximately 16 dyads per cohort, and we will enroll two cohorts every 6 weeks over 24 months. We will provide breakfast and lunch on both days. All intervention activities will occur at research sites in Klipfontein/Mitchells Plain.

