#### Description of the interventions: Informed Motivated Aware and Responsible Adolescents and adults- South Africa (IMARA-SA)

The IMARA curriculum was subject to a comprehensive and systematic adaptation process prior to this RCT. The details of the adaptation process are presented elsewhere [81]. Separate FC and AGYW groups will run simultaneously, cover parallel content, and address individual, social, and structural drivers of HIV-risk (Table 1). Joint activities are designed to enhance FC credibility as a resource for HIV/STI prevention and facilitate practice of new communication skills. Additional activities will address conflict negotiation, assertive communication, and strengthening the AGYW-FC relationship. Interventionists will use interactive and experiential activities to address key constructs. The group format promotes structural change by building community norms for prevention (e.g., HTC and PrEP uptake) and reducing HIV stigma. IMARA-SA’s goals and motto emphasize strong FC-AGYW relationships, sisterhood, empowerment, and motivation for HIV/STI prevention, and build group cohesion. FC and AGYW will sign a pact to confirm commitment to the program. At the end of session 1, participants will receive homework to complete for session 2. Woven throughout IMARA-SA is the impact of mental health, gender-based violence, and alcohol and drug use on HIV-risk.

**Table 1 Tab1:** IMARA-SA Curriculum

Theory	Selected IMARA-SA Activities
Individual Factors	
Knowledge, attitudes, beliefs, skills about HIV, STI, PrEP, HTC	Facts of HIV/AIDS/STI/PrEP/HTC; Prevalence for adolescent girls and young women; PrEP education video; Perceived vulnerability; Personal risk triggers (e.g., people, places, feelings) and risk plans; Demonstrate and practice condom use; De-mystifying HIV testing; Importance of regular HTC and PrEP where appropriate to risk behavior.
Mental health	Destigmatize mental health; Links between mental health problems and HIV-risk behavior; Recognize how feelings trigger risk taking; Teach healthy coping strategies; Recognize the value of the body; Substance use and risk taking; Referrals for counseling
Social Factors	

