### Statistical analysis

We will generate frequencies and summary statistics of predictor and outcome variables to screen and clean the data. We will evaluate randomization by comparing intervention groups on baseline variables using chi-square tests for categorical variables and t-tests or nonparametric Wilcoxon rank-sum tests for continuous variables. In subsequent analyses, we will adjust for predictor variables on which baseline randomization is not successful. We will examine if AGYW who complete the 6- and 12-month assessments differ systematically on baseline data from those lost to follow-up. We will examine correlations among the variables, inspect scale reliabilities to create appropriate scales, and create summary scores as appropriate (e.g., mental health problems). We will use models with random intercepts to account for clustering (if needed) and test the significance of clustering of subjects within groups.

We will analyze binary outcomes using logistic regression and continuous outcomes using linear regression. We will test the effect of the intervention on the primary and secondary outcomes and theoretical mediators, adjusting for confounders and the outcome at baseline as additional independent variables. Analyses combining time points will use generalized linear mixed-models with subject-specific random effects to account for correlation within repeated measurements. We will test an average effect across time points and effects on patterns of change from 6- to 12-months using interactions with time. Survival analysis methods will assess the effect of the intervention on incident STIs, using extended Cox regression models with fixed and time-varying covariates to estimate univariable and multivariable hazard ratios for associations of exposures with incident STI. Treatment effects may differ systematically depending on various factors, such mental health or substance use. We will test mediator and moderator effects according to Baron & Kenny [101] and Cohen & Cohen [102]. We will include interactions between treatment condition and covariates in the GLM, and obtain estimates for regression coefficients of the interaction terms, 95% confidence intervals, and *p*-values for the hypothesis tests.

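### The workshop-group random intercept should be prespecified, not made conditional alongside a significance test that often misses small intraclass correlations

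*Protocol article*

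**What the plan says.** The Statistical analysis section of the Protocol article deals with group clustering in one sentence: "We will use models with random intercepts to account for clustering (if needed) and test the significance of clustering of subjects within groups". It gives no criterion for need other than the test. The outcome models follow: "We will analyze binary outcomes using logistic regression and continuous outcomes using linear regression". The mixed models named there carry subject-level random effects for repeated measurements, which do not represent workshop groups. The Cox model for incident STI has no frailty or robust variance.

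On design, the Randomization section states "We will use a 1:1 randomization allocation to assign FC-AGYW dyads to treatment arm". Treatment is then given in groups: the Abstract (Methods) says that "AGYW-FC dyads will participate in a 2-day group workshop (total 10 h", and Intervention delivery says "We will enroll approximately 16 dyads per cohort, and we will enroll two cohorts every 6 weeks over 24 months". The IMARA-SA description adds: "The group format promotes structural change by building community norms for prevention", with HIV testing and PrEP uptake as its examples.

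The Sample size calculation gives four detectable effects at 80% power or more, with two-sided alpha 0.05:
- RR 0.38 (control 20%) at 80% retention
- RR 0.65 (control 50%) at 80% retention
- d = 0.36 at 75% retention
- HR 0.5 for incidence of 20 to 30% with 25% attrition

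**The concern.** Participants who share a workshop share facilitators, discussion and, by intention, norms. Two of the three primary outcomes (HIV testing and PrEP uptake) are the behaviours those norms are meant to move. Correlation within groups is therefore a consequence of the design, and it should not be established from the trial data before it is allowed for.

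A test of a small variance component with a few dozen small groups and a binary outcome has low power. A non-significant result says little about whether clustering is present. If the intercept is dropped on that basis, the treatment effect is judged against a standard error that is too small. The rule also leaves two possible p-values for each primary outcome, with the choice made after the data are seen.

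**Working it through.** **Inputs.** From the Protocol article: 525 dyads, 1:1; about 16 dyads per cohort; 80% or 75% retention; alpha 0.05 two-sided. Assumptions:
- ICC 0.01 to 0.10, since the article gives none.
- Group size. A cohort may be one group of 16 (525/16 ≈ 33 groups) or may split by arm into about 8 each (about 66 groups). With 80% retention this is about 13 or 6 analyzed per group.
- A 5% threshold for the clustering test, since no criterion is given.

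**Step 1: the plan's own power figures, without clustering.**

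For two proportions, n per arm = [1.96√(2p̄q̄) + 0.84√(p₁q₁ + p₂q₂)]² / (p₁ − p₂)². For two means, n = 2(1.96 + 0.84)²/d².

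| Stated limit | n/arm needed | n/arm retained | Power | Room for a design effect |
|---|---|---|---|---|
| RR 0.38 (20% v 7.6%) | 121 | 210 | 96.0% | 210/121 = 1.74 |
| RR 0.65 (50% v 32.5%) | 124 | 210 | 95.6% | 210/124 = 1.69 |
| d = 0.36 | 122 | 197 | 94.6% | 197/122 = 1.61 |

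The claims of at least 80% power are true, with a margin. Without clustering the 80% limits would be RR 0.51, RR 0.73 and d = 0.28.

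**Step 2: design effect.** DE = 1 + (m − 1) × ICC, and a naive standard error is too small by a factor of √DE.
- ICC 0.02: DE is 1.11 (m = 6.4) to 1.24 (m = 12.8), a factor of 1.05 to 1.11.
- ICC 0.05: DE is 1.27 to 1.59, a factor of 1.13 to 1.26.

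At ICC 0.05 with the larger groups, RR 0.38 keeps 83.6% power and RR 0.65 keeps 82.7% (DE 1.59). For d = 0.36, with 12 of 16 retained, power is 81.8% (DE 1.55).

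**Step 3: the test-then-decide rule.** Beta-binomial simulation with no treatment effect, 40,000 trials per scenario, 20% outcome. Clustering is tested with an ANOVA F test at 5%. If significant, a group-level t test is used; otherwise a naive z test. Each cell gives 16 groups of 13 per arm / 33 groups of 6 per arm.

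| ICC | Clustering detected | Type I, two-step rule | Type I, always ignored | Type I, always modelled |
|---|---|---|---|---|
| 0.01 | 13% / 10% | 5.9% / 5.3% | 6.4% / 5.6% | 5.1% / 5.0% |
| 0.02 | 24% / 15% | 6.4% / 5.5% | 7.8% / 6.1% | 5.0% / 4.9% |
| 0.03 | 38% / 23% | 6.7% / 5.6% | 9.2% / 6.6% | 4.9% / 4.8% |
| 0.05 | 63% / 42% | 6.4% / 5.8% | 12.1% / 7.9% | 5.0% / 4.8% |
| 0.10 | 94% / 82% | 5.3% / 5.6% | 18.5% / 11.3% | 4.9% / 5.1% |

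With a 50% outcome and ICC 0.01 to 0.05, the two-step rule gives 6.3 to 7.3% (groups of 13) and 5.0 to 6.0% (groups of 6).

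**Step 4: the Cox statement.** Power = Φ(√events × |ln HR|/2 − 1.96). HR 0.5 needs 66 events for 80% power. With 25% attrition, 525 × 0.75 = 394 are followed. The article does not say whether 20% is the overall or the control-arm incidence.
- Overall: 394 × 0.20 = 79 events.
- Control arm: the intervention incidence is 1 − 0.8^0.5 = 10.6%, so 394 × (20% + 10.6%)/2 = 60 events.

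| Retained per group, ICC | DE | Power, 20% overall | Power, 20% control arm |
|---|---|---|---|
| no clustering | 1.00 | 87% | 77% |
| 6, 0.02 | 1.10 | 83% | 73% |
| 6, 0.05 | 1.25 | 79% | 67% |
| 12, 0.02 | 1.22 | 80% | 68% |
| 12, 0.05 | 1.55 | 70% | 58% |

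**The case against.** The plan recognizes clustering and names a suitable model. It does not expressly say that the test decides; it says that the model will be used where needed and that clustering will be tested. The test misses clustering mainly when the ICC is small, which is also when the harm is small. When the ICC is large, the test usually finds it and the rule largely corrects itself. All of this stands, and it is why the excess is only one or two percentage points.

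Two stronger readings are tempting, and the document supports neither.

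- A reader might infer that the trial's type I error would be about 8 to 12%. Those figures describe never modelling the group at all (ICC 0.02 to 0.05, groups of 13), which is not the plan. With an ICC of zero there is no inflation.
- A reader might infer from the absence of an ICC or design effect that the power calculation ignored clustering. A condensed article may leave that detail to the full protocol or analysis plan. Moreover, the RR and d limits are conservative by a factor of about 1.6 to 1.7. Whether an unstated allowance explains this cannot be known.

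The objection does not rescue the conditional wording. That wording is a stated rule, not detail left to another document, and always modelling the group holds the type I error at about 5% in every scenario examined.

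**Conclusion.** The point holds as a should-fix and a cheap improvement. Clustering by workshop group is built into the design, yet the group term is conditional. If the test decides, which is the natural reading, it misses clustering in about 60 to 90% of trials at ICC 0.01 to 0.03. At ICC 0.05 it misses it in about 37 to 58%, so for the larger groups it would more often detect than miss it. The resulting type I error is about 5 to 7% instead of 5%.

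This rests on an assumed ICC, an assumed 5% threshold and an uncertain group size (8 or 16 dyads).

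On power, the RR 0.38, RR 0.65 and d = 0.36 statements can stand. With 12 to 13 retained per group they hold up to an ICC of about 0.055 to 0.06. Only the HR 0.5 statement at 20% incidence is exposed. It has room for a design effect of 1.19 if 20% is the overall incidence. If 20% is the control-arm incidence it has none, and falls short (77%) before any clustering.

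**What to change.** In the Statistical analysis section:
- Delete the parenthetical condition and give the significance test no role in choosing the model.
- Prespecify a workshop-group random intercept, or group-robust variance with a small-sample correction, in every primary and secondary outcome model. For the Cox model use a shared frailty or group-robust variance.
- Report the estimated ICC for each primary outcome.

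In the Sample size calculation, leave the RR and d limits as they are. Recheck the HR 0.5 statement: say whether 20% is the overall or the control-arm incidence, and restate power with a design effect over a stated ICC range, for example 0.01 to 0.05, with the group size used.

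The cost is a few lines of text and recording a workshop-group identifier for each dyad. The downside is slightly wider intervals and possibly a less favourable power figure for the Cox analysis.

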## Methods

### Design

This is an individually randomized controlled trial (RCT) of IMARA for 15–19 year-old Black South African AGYW and their FC. AGYW-FC dyads will be randomized to IMARA-SA versus a family-based HP program. All participants will complete baseline, 6-, and 12-month follow-up assessments via audio computerized assisted self-interview technology (ACASI) and provide urine to screen for three sexually transmitted infections (STI). All participants will also be offered HTC and PrEP, and where appropriate (e.g., if HIV/STI positive), will receive free care at the on-site adolescent-friendly reproductive health clinic at the Desmond Tutu Health Foundation (DTHF) and referral to public clinics.

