#### Primary outcomes

At 6-month follow-up, we will examine AGYW STI incidence (gonorrhea, chlamydia, and trichomoniasis), PrEP uptake and 1-month supply of medication, and HTC uptake.

Secondary Outcomes: At 12-month follow-up, we will examine AGYW STI incidence (gonorrhea, chlamydia, and trichomoniasis), PrEP prescription and 1-month supply of medication, and HTC uptake. At 6- and 12-month follow-up, we will assess AGYW sexual behavior (e.g., condom use, substance use during sex, number of partners, concurrent partners), using the AIDS Risk Behavior Assessment, [82] HIV incidence via HTC, and self-reported adherence to ART and PrEP (where appropriate) using Wilson’s 3-item scale [83]. We will use standard cost evaluation methods [84, 85] to assess IMARA-SA’s costs, including personnel time and non-personnel resources (e.g., travel expenses, snacks, incentives, curricular materials).

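### The intervention effect on incident STI is assigned to Cox models with time-varying covariates; post-randomisation survey values there can hide part of the program's effect

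*Protocol article*

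**What the plan says.** All statements are in the protocol article.

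- Statistical analysis, purpose of the model: "Survival analysis methods will assess the effect of the intervention on incident STIs".
- Same sentence, the model: "using extended Cox regression models with fixed and time-varying covariates to estimate univariable and multivariable hazard ratios". The sentence closes by describing these hazard ratios as measures of how exposures relate to incident STI. One model is thus given two tasks: the randomised comparison and exposure associations.
- Design, timing of surveys and tests: "All participants will complete baseline, 6-, and 12-month follow-up assessments via audio computerized assisted self-interview technology (ACASI) and provide urine". The monthly contacts under Retention only update contact details.
- Primary outcomes, behavior: "At 6- and 12-month follow-up, we will assess AGYW sexual behavior". These are the visits that also test for STI.
- Primary outcomes, STI endpoint: "At 6-month follow-up, we will examine AGYW STI incidence (gonorrhea, chlamydia, and trichomoniasis"; the 12-month result is secondary.
- Statistical analysis, other models: "We will analyze binary outcomes using logistic regression and continuous outcomes using linear regression", and "Analyses combining time points will use generalized linear mixed-models with subject-specific random effects to account for correlation within repeated measurements". The section does not say which of the three approaches is primary for STI.
- Mediators and moderators lists knowledge and attitudes, caregiver communication, monitoring, partner communication, stigma, peer influence and substance use. Statistical analysis plans Baron and Kenny mediation tests.

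**The concern.** A randomised arm effect is protected against confounding as long as it is adjusted only for variables fixed before randomisation. A survey value updated at 6 or 12 months is not such a variable. The program is meant to change communication, partner dynamics and risk behavior and, through them, infection. If these enter the model that yields the arm hazard ratio, that ratio no longer measures the whole effect of being offered the program. It estimates something closer to the part not carried by the covariates. In addition, a value recorded at the detecting visit may post-date the infection, so it need not describe behavior before it.

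At stake is a headline result. The Sample size calculation section names STI incidence as the primary outcome and gives its first power statement through a Cox model. A multivariable hazard ratio from the sentence as written could be reported as the effect of the program and understate it.

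**Working it through.** **1. Which survey values can be time-varying (from the visit schedule)**

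| Interval | Value available | Status |
|---|---|---|
| 0–6 months | baseline | pre-randomisation, fixed |
| 0–6 months | 6-month | post-randomisation, same visit as the STI test |
| 6–12 months | 6-month | post-randomisation, precedes the interval |
| 6–12 months | 12-month | post-randomisation, same visit as the STI test |

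For the interval of the primary STI endpoint, a survey covariate is either the fixed baseline value or the value from the detecting visit. In the second interval even a lagged value is post-randomisation.

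**2. The plan's own figure**

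Stated: at least 80% power for a hazard ratio of 0.5, STI incidence 20–30%, 25% attrition, two-sided alpha 0.05. Analysed N = 525 × 0.75 = 394. Schoenfeld: power = Φ(√D × |ln HR| / 2 − 1.96), with D events.

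- Overall incidence 20%: D = 78.75; 8.874 × 0.3466 − 1.96 = 1.116; power 86.8%.
- Overall incidence 30%: D = 118.1; 10.868 × 0.3466 − 1.96 = 1.806; power 96.5%.
- If 20% is the control-arm risk: intervention risk 1 − 0.8^0.5 = 0.1056, mean 0.1528, D = 60.2; power 76.7%.

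The stated figure reproduces when incidence is read as overall. The formula has no mediator in it: it gives power for the whole arm effect, not for one adjusted for post-randomisation behavior.

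**3. Size of the covariate effect (assumed inputs; none is in the article)**

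Assumptions: a risk behavior triples the hazard; its prevalence after randomisation is 50% in control and 30% in intervention; the rest of the effect is a direct hazard ratio of 0.7; the hazard without the behavior is 0.011 per month in control; behavior at 12 months keeps its 6-month value with probability 0.7 and is otherwise redrawn; baseline behavior is independent of later behavior.

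By hand, the whole effect early in follow-up is 0.7 × (0.7 + 0.3 × 3) / (0.5 + 0.5 × 3) = 0.7 × 1.6 / 2.0 = 0.56.

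Simulation of 10 sets of 20,000 subjects gave 12-month risks of 22.5% (control) and 13.4% (intervention), and these arm hazard ratios:

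| Covariate in the model | Cox, Efron | Cox, Breslow | Complementary log-log |
|---|---|---|---|
| none | 0.562 | 0.577 | 0.561 |
| baseline | 0.562 | 0.577 | 0.561 |
| lagged one visit | 0.580 | 0.595 | 0.580 |
| detecting visit | 0.702 | 0.717 | 0.701 |

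Share of the log effect lost with the detecting-visit value: 1 − ln 0.702 / ln 0.562 = 1 − 0.354/0.576 = 0.39.

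For a range, suppose a share m of the log hazard ratio runs through the covariate and is fully adjusted away. The adjusted ratio is then HR^(1 − m). With HR 0.50: m = 0.25 gives 0.59, m = 0.5 gives 0.71, m = 0.75 gives 0.84.

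**4. Visit dating alone**

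Place events at 6 and 12 months, constant hazards, true HR 0.50, no time-varying covariate. Breslow's large-sample limit is here the ratio of interval risks.

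- Control risk 20% at 12 months: 6-month risks 1 − 0.8^0.5 = 0.1056 and 1 − 0.8^0.25 = 0.0543; ratio 0.514.
- Control risk 30%: 0.1633 and 0.0853; ratio 0.522.
- Efron: 0.500 in both. Complementary log-log: 0.500. At a true ratio of 1, all give 1.00.

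In 500 simulated trials per setting (N = 525, 25% missing the 12-month visit, visits on time or up to 2 months late, true HR 0.50), mean ratios were 0.51–0.52 (Breslow), 0.49–0.51 (Efron) and 0.49–0.50 (complementary log-log), with interval coverage of 92–95%. At HR 1, rejection rates differed between methods by at most 1.4 percentage points within any setting.

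**The case against.** The strongest reply is that the sentence ends in exposure associations, where time-varying behavior is legitimate. It also promises univariable hazard ratios, and a univariable arm ratio contains no mediator. For tests on primary and secondary outcomes, the section speaks of adjusting for confounders and the baseline outcome, and it handles mediators separately. Logistic regression already covers STI at 6 months. The article lists no covariates for the Cox model, and the size of the shift rests on assumed inputs.

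Most of this stands and limits the severity. It does not remove the point, because the same sentence opens by giving this model the intervention effect and nothing in it separates the two tasks.

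Two stronger readings are tempting:

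- A reader might infer that the plan takes visit dates as infection times and uses covariates from the detecting visit. The article states neither. Event dating, tie handling and lags commonly sit in the statistical analysis plan, so their absence is not a fault.
- A reader might infer that a Cox model on two-visit data materially biases the arm hazard ratio. The figures do not support this: there is practically no shift with Efron ties, a shift to about 0.52 at most with Breslow ties, and none under the null. Visit timing that differed by arm could matter, but the article gives no sign of it.

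**Conclusion.** The point holds for the covariates. As written, the model said to assess the intervention effect on STI admits post-randomisation covariates, many of them variables through which the program is expected to work. A multivariable arm hazard ratio from it can be pulled toward 1: from 0.56 to 0.70 in the assumed scenario, about 39% of the log effect. The direction follows if the program lowers risk partly through these covariates; the size depends on how much of the effect they carry and on which visit's value is used. A univariable ratio, or a 6-month logistic model adjusted only for baseline variables, escapes the problem.

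Replacing Cox by a discrete-time model would not cure it, since the complementary log-log model gives the same 0.70. The grouped nature of the infection times is a minor matter of fit between model and data, not a material bias.

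**What to change.** 1. State that the intervention effect on incident STI is estimated with arm and baseline covariates only, whichever model is used.
2. Move time-varying covariates to separate exposure-association or mediation models, lagged by one visit: the baseline value for months 0–6 and the 6-month value for months 6–12. Label those hazard ratios as not being the effect of the program.
3. Minor: use a complementary log-log model for first STI by visit interval, which still yields a hazard ratio. A participant who misses the 6-month visit contributes one 0–12 month interval. If Cox is kept, specify Efron ties.

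Cost: a few sentences in the analysis plan and changes to code. No new data, visits or participants are needed.

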#### Mediators and moderators

We will assess HIV/STI knowledge, attitudes, beliefs, and skills, [86–88] mental health, trauma, and intimate partner violence exposure, [89–92] PrEP knowledge and attitudes, quality and quantity of FC-AGYW communication, [32, 93, 94] parental monitoring, [95] and warmth and closeness in the relationship, [96] gender dynamics and partner communication, [94, 97–99], HIV/AIDS and PrEP stigma, [100], peer influence, [82] and substance use [82]. At 6- and 12-month follow-up, control group participants will indicate if they heard about IMARA-SA (yes/no) and what they heard (open-ended) to assess contamination.

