### Sample size calculation

Power analyses determined the sample size needed to compare the effect of IMARA-SA and control interventions on AGYW HIV/STI incidence and PrEP and HTC uptake. Because binary outcome variables pose the greatest challenge for power, we evaluated power for STI incidence (yes/no)—our primary outcome—across a range of prevalence estimates over 12-months. All calculations used a 2-sided test with alpha = .05. Based on data in the Plus Pills study, [103] using a Cox proportional hazards model with a range of incidence estimates, we will have ≥80% power to detect hazard ratios ≤0.5 for STI incidence ranging from 20 to 30%, even with 25% attrition. Effect sizes for binary outcomes is given in terms of the relative risk (RR), where RR = 1 indicates no treatment effect. A RR < 1 indicates a protective effect of the intervention. With 80% retention, we will have ≥80% power to detect RRs ≤ 0.38 when the proportion in the control group is 20%, and RRs ≤ 0.65 when the proportion in the control group is 50%. We also calculated the standard effect size (d) in standard deviations for group mean comparisons with 80% power for continuous outcomes, where d = 0 is defined as no treatment effect. We will be able to detect a small to medium effect size (d = 0.36) even with 75% retention. Low HIV incidence among AGYW (2.54%) per year will allow us to explore incidence, but we do not expect sufficient statistical power to test intervention effects on HIV incidence.

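### Causal-steps mediation testing ties any mediation finding to a significant total effect and gives no indirect-effect estimate; it loses substantial power when the STI effect is smaller than planned

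*Protocol article*

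**What the plan says.** All from the protocol article.

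- **Method.** Statistical analysis: "We will test mediator and moderator effects according to" two cited sources, of which the first is the Baron-Kenny causal-steps method.
- **Paths tested.** The same section says "We will test the effect of the intervention on the primary and secondary outcomes and theoretical mediators". That covers the arm-to-outcome and arm-to-mediator regressions. Binary outcomes are to be analysed by logistic regression, and incident STI also by extended Cox models.
- **Intervals promised.** At this point the plan will "obtain estimates for regression coefficients of the interaction terms, 95% confidence intervals" and p-values. These belong to moderation. No estimate, test or interval for an indirect effect is named.
- **Mediators.** Mediators and moderators lists knowledge, stigma, parental monitoring, "quality and quantity of FC-AGYW communication" and others.
- **Timing.** Assessments are at baseline, 6 and 12 months. For the primary outcomes, "At 6-month follow-up, we will examine AGYW STI incidence" along with PrEP and HIV testing and counseling (HTC) uptake. The same three outcomes at 12 months are secondary.
- **Power.** Sample size calculation: "All calculations used a 2-sided test with alpha = .05". The plan claims "≥80% power to detect hazard ratios ≤0.5 for STI incidence ranging from 20 to 30%, even with 25% attrition", and at least 80% power for RR 0.38 or lower at a 20% control proportion with 80% retention. These figures refer to a 12-month horizon.

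**The concern.** Causal steps begins with a significant total effect of arm on outcome. If that test fails, the procedure reports no mediation, however clearly the programme moves the mediator and the mediator predicts the outcome. The test most likely to fail here is the total effect on STI, because the stated power covers only large effects. The one prior effect the article gives for the programme, a 43% reduction at one year (RR about 0.57, Background), is weaker than the planning effects at 20% risk.

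The method also yields a yes/no answer rather than an effect size. With a logistic outcome model, the change in the arm coefficient after adding the mediator is not a clean measure of mediation, because odds ratios are non-collapsible: the coefficient can shift even when nothing is mediated.

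At stake is what the trial can say about mechanism. The programme is built on caregiver communication, knowledge and stigma, so a null mediation result produced by the testing rule could be read as evidence against that theory.

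**Working it through.** **1. The plan's own power for the total effect.** 525 × 0.80 = 420 analysed, 210 per arm under the 1:1 allocation ("We will use a 1:1 randomization allocation to assign FC-AGYW dyads to treatment arm"); two-sided alpha 0.05.

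- RR 0.38 at 20% control compares 0.20 with 0.076. n per arm = [1.96√(2p̄q̄) + 0.84√(p₀q₀ + p₁q₁)]² / (p₀ − p₁)², with p̄ = 0.138, gives 121 for 80% power. At 210 per arm power is 96%. The claim of at least 80% is therefore true, but 0.38 is not the limit: the plain formula reaches 80% at RR 0.51. The ratio 210/121 = 1.7 suggests a variance inflation that the article does not state.
- HR 0.5 needs 4(1.96 + 0.84)²/(ln 0.5)² = 66 events (Schoenfeld). With 25% attrition, 20% overall incidence gives 525 × 0.75 × 0.20 = 79 events and 87% power. If 20% is the control-arm incidence, there are 60 events and 77% power.
- At the prior RR of 0.57, power for the total effect is 68% at 20% control risk and 88% at 30%. With the implied inflation of 1.7 these become 46% and 67%. Without inflation, power falls below 50% from RR 0.65 at 20% risk and from RR 0.73 at 30%.

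**2. Cost of the total-effect requirement.** Simulation with 210 per arm. Mediator M = a × arm + standard normal error. Outcome: logit P(STI) = b₀ + b × M + c × arm, with b₀ set to give the control risk and c to give the total RR. Causal steps requires the total effect, the arm-to-mediator path and the mediator-to-outcome path all to be significant at 0.05. The joint test requires only the two paths. The article gives no path sizes, so a = 0.4 SD and b = -0.5 per SD are assumptions. With 1,500 runs the Monte Carlo standard error is at most √(0.25/1500) = 1.3 points.

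| Control risk | Total RR | Causal steps | Joint test | Loss (points) |
|---|---|---|---|---|
| 20% | 0.47 | 80% | 91% | 11 |
| 20% | 0.59 | 61% | 94% | 33 |
| 20% | 0.73 | 30% | 95% | 65 |
| 20% | 0.85 (no direct effect) | 11% | 95% | 84 |
| 10.6% | 0.56 | 31% | 77% | 46 |

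The 10.6% row converts a 12-month risk of 20% to 6 months under a constant hazard: 1 − 0.80^0.5 = 0.106.

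**3. Sensitivity to the assumed path.** With a = 0.36 (the plan's detectable standardised difference), b = -0.5 and 2,000 runs:

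| Control risk | Total RR | Causal steps | Joint test |
|---|---|---|---|
| 20% | 0.38 | 86% | 89% |
| 20% | 0.50 | 74% | 89% |
| 20% | 0.57 | 61% | 90% |
| 20% | 0.70 | 34% | 91% |
| 30% | 0.57 | 83% | 94% |
| 30% | 0.70 | 55% | 95% |
| 10.6% | 0.57 | 27% | 74% |
| 16.3% | 0.57 | 50% | 87% |

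(16.3% = 1 − 0.70^0.5.) The pattern is the same: a small loss at the planning effects, and a large one as the total effect weakens or the risk falls.

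**4. False positives.** With no arm effect on the mediator and no total effect, the joint test was positive in 5% of runs, so its advantage is not bought by a raised error rate in that setting. Confounding is a different matter. Take a mediator with no effect on STI but an unmeasured cause shared with it (assumed 0.4 or 0.5 SD on the mediator and log-odds -0.5 or -0.7 on STI). The joint test then declared mediation in 35% and 74% of runs, against 2% and 3% for causal steps. When the programme had a real direct effect and the mediator was confounded, causal steps also declared false mediation, in 37% of runs.

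**The case against.** **At the planned effects the method mostly works.** A reader might infer that causal steps will usually miss real mediation. The documents do not support that: it succeeds in 86% of runs at RR 0.38, 74% at RR 0.50, and 83% at RR 0.57 with 30% control risk. A miss becomes more likely than not only from about RR 0.65 at 20% risk, at 6-month risks near 10%, or at RR 0.57 with 20% risk if the implied inflation applies. This objection stands and limits the size of the point.

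**The total-effect requirement may give protection.** It suppresses false mediation when there is little total effect. But it protects only by being rarely passed; once the programme has a real direct effect, confounding misleads causal steps too. What stands is that dropping the requirement without a confounding sensitivity analysis would be a poor exchange.

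**Timing.** A reader might infer that 6-month mediators will be paired with 6-month outcomes, leaving direction unclear. The article states no such pairing, and its three visits allow a lagged analysis. Lagging is therefore a preference in the fix, not an error in the plan.

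**Detail left to the SAP.** Bootstrap, lag and sensitivity analyses can properly sit there. The article also does not itself say that testing stops without a significant total effect; that condition comes with the method it names. But naming the method is a choice the article makes, and that choice is the subject here.

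**Scope.** The power loss is shown for STI only. For HTC and PrEP uptake it depends on effects and control proportions not examined here. The size of the non-collapsibility shift was not quantified either.

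**Conclusion.** The point holds as a secondary-level weakness. The named method makes a mediation finding depend on a significant total effect and provides no indirect-effect estimate or interval. For STI at 20% control risk the cost is about 11 points of power at RR 0.47, 33 at RR 0.59, and 65 to 84 at RR 0.73 to 0.85. At a 6-month risk of 10.6% it is 46 points at RR 0.56. These figures rest on assumed path sizes, a perfectly measured and unconfounded mediator, 420 analysed without variance inflation, and, for the 6-month figure, a constant hazard. The comparator is a joint significance test, not the bootstrap interval recommended below. Mediation is not among the study objectives or the primary and secondary outcomes, so the effectiveness and cost-effectiveness conclusions are unaffected.

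**What to change.** - State that mediation will be assessed without requiring a significant total effect.
- Estimate the indirect effect directly, with a bootstrap 95% CI. For binary outcomes, use a counterfactual (natural indirect effect) or risk-difference scale instead of comparing log odds ratios with and without the mediator.
- Prefer the 6-month mediator with the 12-month outcome, adjusted for the baseline values of both. Treat any same-visit analysis as descriptive.
- Add a sensitivity analysis for unmeasured mediator-outcome confounding. Randomisation does not protect that path, and step 4 of the working shows how easily it misleads.

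The cost is SAP wording and a little more analysis work, using data already scheduled. Attrition leaves slightly fewer participants at 12 months than at 6.
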